### 2.3. Data Collection

To preserve the confidentiality of the participants’ data, the researchers commit to complying with Organic Law 3/2018, of December 5th, on the protection of personal data and the Royal Decree that enforces it (RD 1720/2007). The participants will receive a code that will be related to the personal data only in a coding sheet. The evaluations will be conducted by a blinded researcher ([name]), who will initially collect the data of the participants in a data collection sheet: age, body mass index, data and type and level of spinal cord injury, pathologies or complications derived from the injury, allergies, pregnancies, type of deliveries and other diseases. Then, the participants trained by this researcher will complete the FSFI questionnaire, the SQOL-F, and the quantitative sensory test at the beginning of the treatment (V0, before the participants are randomized to any of the 3 groups), after the treatment (V1), and at 3 months (V2), 6 months (V3) and 12 months (V4) after the end of the treatment. [name] will be previously trained to standardize the measurements and will be blinded throughout the entire study to the randomization of the participants.

### 2.4. Data Analysis

Firstly, a test will be performed to determine the efficacy of the randomization of the baseline characteristics of the participants in the 3 groups through the Shapiro-Wilk test and normal distribution diagrams.

Secondly, we will establish the rate of adherence of the different participants randomized to each of the groups and their percentage of abandonment, comparing their effect through the *t*-test or Mann-Whitney *U*-test to determine whether the groups differ in the demographic variables in V0.

Thirdly, the comparisons to determine the effect of the interventions on FSFI, SQOL-F and the quantitative sensory tests in different time points will be analyzed with ANOVA, or Kruskal-Wallis for non-parametric samples, using the Bonferroni method for the multiple comparisons between different evaluation time points. The results will be considered statistically significant if *p* < 0.05. Moreover, the differences between each evaluation after the intervention and the arousal and orgasm before the intervention will be recorded in binary variables of “improvement of arousal/orgasm”, with values 0 (same or lower arousal) and 1 (greater arousal). Thus, improvement in all variables will be compared with the rate of participants who increase their sensation in the three groups through the risk ratio and the χ^2^ test. The data analysis will be carried out using the SPSS software v.25.0 (IBM, New York, United States).

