## 2. Materials and Methods

A protocol of a randomized clinical trial is presented with a blind randomization in the evaluation ([name]) and in the data analysis ([name]). The present protocol was registered in the platform https://register.clinicaltrials.gov/ (accessed on 16 November 2021) (NCT05122325). The study will be carried out according to guidelines and recommendations established for protocols by the SPIRIT statement [27].

The study is aimed at women with incomplete SCI, after which they had presented some type of SD. The candidates who participate in the study must meet the following inclusion criteria: women with American Spinal Injury Association or ASIA impairment B, C or D incomplete SCI (with preservation of the sacral arch and non-absent sensory evaluation of the lower dermatomes) below T6; aged 18–60 years without menopausal values of the follicle stimulating hormone (31–134 U/L) in a normal analysis; who present some type of SD secondary to SCI with at least 12 months of evolution; who live in Spain and are willing to go to the center of evaluations and treatments; and who sign the informed consent.

On the other hand, the study will exclude those women with active pregnancy and those who present pre-existing pathologies in the genital area, genital malformation, previous neurosurgery that affects the capacity of genital response, SD prior to the SCI, pressure ulcers, severe medical disease or any type of pathology in which the use of low frequency is contraindicated. In addition, the study will also exclude those with a psychiatric disorder or dependency on narcotics, and those who use selective serotonin reuptake inhibitors, antipsychotics or other drugs that affect the sexual response.

Regarding the sample size predicted for this study, 15 subjects were estimated for each group, with an effect size of 1.1, Df 28, α = 0.05, power (1 − β) = 0.80 (1 − β err prob) = 0.80u. Moreover, 20% more women will be recruited in order to consider the possible heterogeneity of the group and participants lost during the course of the study. Thus, a total of 54 women (18 women per group) will be recruited.

The project will be advertised in social networks, as well as in all the entities that belong to the ASPAYM (Association of people with spinal cord injury and other physical disabilities) in Spain.

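### Section 2.4 uses a normality test to judge whether randomisation worked, and names only two-sample tests for the adherence, abandonment and baseline step of a three-arm trial

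*Protocol article*

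**What the plan says.** Section 2.4 (Data Analysis) of the protocol article sets out three steps.

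- **Step 1, randomisation.** A test will "determine the efficacy of the randomization of the baseline characteristics of the participants in the 3 groups through the Shapiro-Wilk test", together with normal plots.
- **Step 2, adherence and abandonment.** Adherence and the percentage of abandonment are to be established in each group, "comparing their effect through the *t*-test or Mann-Whitney *U*-test to determine whether the groups differ in the demographic variables in V0".
- **Step 3, efficacy.** FSFI, SQOL-F and the sensory tests "will be analyzed with ANOVA, or Kruskal-Wallis for non-parametric samples", "using the Bonferroni method for the multiple comparisons between different evaluation time points". The binary improvement variables are compared across the three groups by risk ratio and chi-squared test. The threshold is given here: "The results will be considered statistically significant if *p* < 0.05".

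Section 2 (Materials and Methods) fixes the design at three equal arms: "a total of 54 women (18 women per group) will be recruited". The Abstract announces that adherence will be evaluated. The limitations paragraph in section 3 warns that abandonment is high in this population.

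**The concern.** Step 1 gives a named test a purpose that it cannot serve. Shapiro-Wilk asks whether one sample could have come from a normal distribution. Adding a constant to every value in an arm leaves its statistic unchanged, so a difference in level between arms is invisible to it when it is applied arm by arm. Read as written, the check can cast doubt on randomisation because a well-balanced variable is skewed, and can reassure when one arm is far from the others.

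Step 2 names two tests that each take two samples, in a trial with three arms. It does not say which pairs would be compared, and states no correction for several pairs. It also joins adherence, abandonment and baseline demographics in one sentence, although abandonment is a yes/no fact about each woman and neither named test is designed for that.

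At stake are the reading of the baseline table and the comparison of adherence and dropout between a clinic-based stimulation arm, a vibrator arm and a sham arm. With 18 women per arm and abandonment expected, readers will want both reported soundly.

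**Working it through.** **Inputs from the protocol article.** Three arms of 18 (section 2); significance at p < 0.05 (section 2.4); Shapiro-Wilk for step 1 and t-test or Mann-Whitney for step 2 (section 2.4). Bonferroni is stated only between evaluation time points.

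**Assumptions, not in the document.** The shape of the baseline variables (normal, or lognormal with log-scale SD σ), the size of any shift, and, for step 2, that all three pairs of arms are tested without correction. Shapiro-Wilk is applied in each arm. The simulation used 5,000 trials per scenario.

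**The plan's own figure.** The plan gives no error rate for these checks. Its only related figure is the sample size, which reproduces: a two-sided two-sample t-test with effect size 1.1 and 15 per group (df = 2 × 15 − 2 = 28) has power 0.828. Adding 20% gives 15 × 1.2 = 18 per arm and 3 × 18 = 54. That calculation does not depend on steps 1 or 2.

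**Step 1: what Shapiro-Wilk responds to.** With three independent arms of normal data, the chance of at least one rejection is 1 − 0.95³ = 14.3%, whatever the arm means are.

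| Scenario, 3 × 18 | Shapiro-Wilk rejects in at least one arm | One-way ANOVA rejects |
|---|---|---|
| Normal, balanced | 14.1% | 5.0% |
| Normal, one arm shifted by 1.1 SD | 15.1% | 92.5% |
| Lognormal (σ = 0.8), balanced | 99.2% | 3.7% |

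The gap between 14.1% and 15.1% is simulation noise. Its standard error is √(0.141 × 0.859/5000 + 0.151 × 0.849/5000) ≈ 0.7 percentage points, and both values lie close to the theoretical 14.3%. ANOVA is in the table only to show that the shift is large enough for a test of location to find.

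The rate for skewed but balanced data depends on the assumed skewness: about 52% at σ = 0.3, about 97% at σ = 0.7 and about 99% at σ = 0.8. The document gives no basis for choosing among these.

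**Step 2: two-sample tests in three arms.** Three uncorrected pairwise t-tests on balanced normal data gave at least one false difference in 12.4% of trials per variable. This is below the 14.3% that three independent tests would give, because the pairs share arms. With Bonferroni over the three pairs the rate was 4.3%; with ANOVA it was 5.0%.

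**Step 3 beside step 2.** ANOVA, Kruskal-Wallis and chi-squared all accept three groups. The section therefore uses three-group methods for efficacy and two-group methods for adherence and baseline, without giving a reason.

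**The case against.** The best defence is that step 1 is a slip of description. The later steps offer parametric and non-parametric pairs of tests, and choosing between them is the usual job of a normality test. The section also attaches no action to the Shapiro-Wilk result: no re-randomisation, adjustment or change of outcome. This limits the consequence, but the sentence still states a purpose that the test cannot serve, and nothing elsewhere in the article corrects it.

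Step 2 can also be read more kindly. It may mean that women who stay are compared with women who leave on V0 demographics. A two-sample test is then legitimate for continuous variables, and abandonment is the grouping factor and not the outcome. Or it may mean pairwise arm comparisons, each valid on its own. Both readings are possible, so it would be too strong to say that this step gives wrong answers. What stands is that the sentence does not settle what is compared. If it means comparisons between arms, the error over pairs is uncorrected and the tests do not fit abandonment.

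A reader might infer that the trial as a whole compares three arms with two-sample tests. The document does not support that: the efficacy outcomes have three-group tests. A reader might also take a near-certain false alarm for skewed variables as a property of this trial. It is not, since the rate moves from about half to nearly all trials with the assumed skewness.

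Finally, adherence and abandonment are absent from the outcome list in section 2.2. They are supporting results, although the Abstract does announce adherence as something to be evaluated.

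**Conclusion.** The point holds in two parts of unequal strength.

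1. **Shapiro-Wilk as a check of randomisation is wrong as written.** Its rejection rate is about 14 to 15% whether the arms are balanced or one is shifted by about 1 SD (normal data, 18 per arm, at least one rejection in three arms). It therefore carries no information on balance. A balanced skewed variable is often flagged, at a rate that cannot be fixed from the document.
2. **The adherence, abandonment and V0 sentence is unclear and, read as arm comparisons, ill-fitting.** On that reading there are about 12% false positives per variable if all three pairs are tested uncorrected, and neither named test suits a yes/no outcome.

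The sample size and the efficacy comparisons do not rest on either step. The correction is worth making because the fault is plain and costs almost nothing to remove, not because the main result is threatened.

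**What to change.** Reword the first two paragraphs of section 2.4:

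- State that Shapiro-Wilk and normal plots serve only to choose between parametric and non-parametric methods.
- Replace the test of randomisation with a descriptive baseline table by arm (mean and SD, or median and interquartile range, and counts), without significance tests.
- Compare abandonment across the three arms with a 3×2 exact or chi-squared test.
- Compare the number of sessions or uses completed across the three arms with Kruskal-Wallis or ANOVA.
- If completers are to be compared with dropouts on V0 variables, say so in a separate sentence. The t-test or Mann-Whitney test can then stay for the continuous variables.

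The cost is the wording of two paragraphs. Design, recruitment, data collection, sample size and the efficacy analysis do not change.

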### 2.5. Ethical Issues

This intervention proposal has been sent for approval to the University of Malaga Clinical Research Ethics Committee (153/2021). The ethical principles of the declaration of Helsinki will be followed throughout the entire study. The confidentiality of the study data will be a priority.

## 3. Discussion

After evaluating the effectiveness of an educational program plus either intervention (TTNS or vibration) in women with SD after SCI, it is expected to observe improvements in sexual function and the quality of life in both intervention groups. However, considering the neuropathophysiology of the injury, differences in arousal and orgasm will be also expected.

Regarding sexual function, the sympathetic routes mediate psychogenic arousal and require intact thoracic-lumbar segments (T11—L2). It is fundamental that women have their sacral segment intact (S2—S4/5) in order to reach orgasm. However, despite complete SCIs, orgasmic sensations persist and are accompanied by predominantly sympathetic signs, followed by parasympathetic signs (after orgasm) [15]. Therefore, the application of low-frequency genital vibration, due to its hyperemia effect, can improve relaxation and, thus, orgasm in women with SCI [22,23]. On its part, TTNS has shown excitatory effects through sensory afferences [20]. Consequently, the aim is to balance the excitatory and inhibitory impulses (sympathetic and parasympathetic mediation), which results in a possible improvement of vaginal arousal and lubrication [16].

Most of the studies found in the literature on treatments to improve the sexual function refer to transcutaneous tibial nerve stimulation [38,39,40]. However, due to the risks derived from needle puncture and its possible rejection, transcutaneous stimulation is proposed, since an access route has been demonstrated with similar effectiveness and no adverse effect associated that can generate discomfort in the participants [41,42]. Moreover, the literature shows a majority of studies on SD in SCI with only males [43]. Nevertheless, a qualitative study reported that sexuality is still an important and valued aspect of the female identity after SCI [44]. The same authors assert that sexual activity, although altered, is still pleasing and gratifying. Therefore, it is essential to study different interventions that help women to reestablish their sexual activity and improve their quality of life after SCI.

## 4. Conclusions

This protocol will analyze, in a poorly studied field, interventions for sexual dysfunction in women after SCI to promote the social participation of the women included in this research. The randomized design will allow determining the specific field for improvement of each intervention in SD. The educational handout designed as a common guideline will benefit all the participants, regardless of the group to which they are assigned.

## Figures and Tables

**Figure 1 ijerph-19-01478-f001:**
[figure not shown]
Flow chart of study participants.

**Figure 2 ijerph-19-01478-f002:**
[figure not shown]
Transcutaneous tibial nerve stimulation (TTNS) electrode placements.

**Table 1 ijerph-19-01478-t001:** Educational handout common guideline.

New Sources of Excitation after Spinal Cord Injury	
Improving your sexuality after spinal cord injury	If you wish to have sex alone or with your partner, first of all, it is important to try to find positions that help you to manage your body’s spasticity. You can try this in your wheelchair or in the shower. On the other hand, we want to show you a different way to enjoy sexuality by rediscovering yourself; therefore, here we list two activities to do alone and/or with your partner.
Discover your erogenous zones	Sexuality is something natural in human beings and therefore, after the spinal cord injury, the brain has the capacity to adapt to the new situation, favoring the appearance of new erogenous zones or strengthening those it had before. Rediscover yourself and look for new areas of pleasurable sensation that will serve to initiate sexual arousal, which requires you to explore your whole body, although you can focus on your ears, nipples, neck and hair. With this exploration you can elaborate a body map of sensitive areas, classifying those with which you have response of sexual arousal. ^1^
Rediscover your body	To rediscover your body, you can use the somatosensory massage. It will last approximately 30 min and will be performed very slowly. It is recommended as an initiation to sexual intercourse. You can do it yourself, with the limitation that there will be areas that you do not cover, or with the help of your partner. It can be done in underwear or completely naked, as you feel more comfortable. Talcum powder or oil can be used in a pleasant environment with lights or scents that allow you to concentrate on the sensations of touching different parts of your body. Once you start, it is important to avoid interruptions.
Steps to follow in somatosensory massage	Lie on your stomach and touch all areas of your body to improve your overall proprioception. It is important to mention in a soft and pleasant voice the part of the body over which we are sliding our fingers. Start with the foot and very slowly go over all the skin without exerting pressure, then continue along the leg, thigh, genial area, buttocks, opposite leg, back, shoulder, arm, forearm, hand, fingers, neck and head. Afterwards, lie on your back and again touch the lower limbs, genital area, abdomen, breasts, upper limbs, neck and head. In the genital area, when facing upwards, it is important to focus on touching all the areas that make up the genital area: starting with the labia majora, labia minora, entrance to the vagina and finally removing the clitoral hood to gently caress the clitoris.

^1^ Greater (+++) or lesser (+) response of sexual arousal.

## Data Availability

Data will be held securely by the research team and may be available upon reasonable request and with relevant approvals in place.
